## **Statistical Considerations**

The sample size of two Vi-DT groups is decided based on the immunogenicity equivalence and safety data requirement. The immunogenicity subset in adult participants, N=250 per group, will provide 94% power to show equivalence of geometric mean titres (GMT) of anti-Vi IgG at 4 weeks (28 days) after vaccination of Vi-DT(MD) and Vi-DT (SD), with the equivalence margin of 0.67 to 1.5 following WHO recommendation per (WHO TRS 924). Coefficient of variation (CV) of immunogenicity titre is conservatively assumed as 2.0 based on data from IVI T001 (i.e., Vi-DT phase 1 in children, adolescents, and adults in the Philippines) and IVI T002 (i.e., Vi-DT Phase 2 in infants/toddlers in the Philippines) studies with type 1 error rate of 0.05 and 10% drop out rate are also assumed. This sample size of N=250 will provide 95% power, for equivalence tests of seroconversion rate between two formulations of Vi-DT with equivalence margin of [-10%, 10%]. In this calculation, 90% of sero-conversion rate in Vi-DT is assumed (based on IVI T001) with type 1 error rate of 0.05. The sample size of N=300 control (Meningococcal vaccine) is calculated to observe at least one events with 1% of the upper limit of 95% CI for any adverse event of incidence according to rule of three.

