## 5.2 METHODOLOGY

This is a multicenter, randomized, observer-blinded, controlled, immune equivalence study of a multi-dose formulation with 2PE preservative of SK bioscience Vi-DT (MD) compared to single dose formulation without preservative of SK bioscience Vi-DT (SD) in participant (6 months - 45 years) including safety population. The Vi-DT vaccines will be administered to 1,500 healthy participants of 6 months to 45 years of age and followed up for 24 weeks after the injection for safety. Adult participants (N=500) will be followed up additionally for immunogenicity 4 weeks post vaccination and all participants till 24 weeks for safety post single dose of the MD & SD formulations. 300 healthy participants will be given control vaccine (Meningococcal conjugate Vaccine) to check the background safety events. The primary objective is to demonstrate the equivalence of immunogenicity as measured by anti-Vi IgG GMT titer 4 weeks after a single dose of MD/SD formulation in adults. The secondary objective is to demonstrate the equivalence of immunogenicity in terms of seroconversion rates as measured by anti-Vi IgG ELISA antibody titers, 4 weeks after a single dose of MD/SD formulations in adults. A descriptive evaluation of safety at 4 and 24 weeks post single dose of (MD/SD/ Meningococcal conjugate Vaccine ) will be performed. The Vi-DT vaccine from both MD & SD formulations will be administered as a single dose of 25 µg.

Eligible participants enrolled into the study will be randomized into one of the three study groups within each age stratum of 6 months to less than 2 years, 2 to less than 18 years, and 18 to 45 years. Participants will be observed at the study site for 30 minutes after vaccination for immediate safety assessment. Solicited adverse events will be recorded on a diary card during 7 days after vaccination. Unsolicited adverse events will be recorded during the 4 weeks after vaccination. Serious adverse events will be recorded during the entire study period. With the exception of designated study site personnel responsible for vaccine administration, study

investigators, study nurses, and those assessing clinical outcomes, and data analysts will be blinded to vaccine allocation until database lock for the final analysis.

Blood samples will be collected at baseline prior to vaccination and at 4 weeks post vaccination from adult participants (18-45 years) only for immunogenicity assessment.

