### **Age Strata reassignment (Stratawise Enrollment number of subject)**

The initial enrollment plan required an equal number of subject enrollment from each age stratum and the current plan allows for the adjustment of the required number of subjects in each stratum during the enrollment period.

Post-dose blood sample could not be collected from the enrolled adults stratum due to COVID-19. As of 13MAR2020, the Philippines government has imposed a country-wide lock down (as a result of the COVID-19 pandemic) which has impacted the ongoing activities for the clinical trial. Subjects enrollment as well as planned visit 4 blood collection (the post-vaccination blood

sample from adults stratum) has been impacted because of the lockdown. In this situation, there will be additional subjects enrollment into the adults stratum so as to keep the initial planned statistical power for immune equivalence test as planned initially, while reducing the enrollment of subjects in the other two age strata. This will ensure the total number of subjects at 1800 as per original plan.

Due to city lock down those subjects whose blood sample could not be collected on V4, their post- vaccination blood sample would not be collected when lock down is lifted. This will be considered as deviation and will be informed to respective ethics committee.

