## 11 STATISTICAL CONSIDERATIONS

### 11.1 SAMPLE SIZE

A total of 1800 participants (1500 in Vi-DT test arm and 300 in control arm) aged 6 months to 45 years will be enrolled in this study. Participants will be randomized equally into first 2 groups of 750 participants each and third group with 300 participants within each age strata of 6 months to less than 2 years, 2 to less than 18 years and 18 to 45 years.

The sample size of two Vi-DT groups is decided based for the immunogenicity equivalence and safety data requirements. The immunogenicity subset in adult participants, N=250 per group,

will provide 94% power to show equivalence of geometric mean titres (GMT) of anti-Vi IgG at 4 weeks (28 days) after vaccination of Vi-DT (MD) and Vi-DT (SD) , with the equivalence margin of [0.67, 1.5] (WHO TRS 924). Coefficient of variation (CV) of immunogenicity titre is conservatively assumed as 2.0 based on IVI T001 and T002 studies at type 1 error rate of 0.05, and 10% drop out rate is also assumed. This sample size of N=250 will provide 95% power, for equivalence tests of seroconversion rate between two formulations of Vi-DT with equivalence margin of [-10%, 10%]. In this calculation, 90% of sero-conversion rate in Vi-DT is assumed (based on IVI T001) with type 1 error rate of 0.05. The sample size of N=300 control (Meningococcal vaccine) is calculated to observe at least one events with 1% of the upper limit of 95% CI for any adverse event of incidence according to rule of three.

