## 11.3 STATISTICAL HYPOTHESES

The statistical hypothesis for the primary objective is to demonstrate equivalence of two Vi-DT formulations (MD vs. SD) using GMT.

- Anti-Vi IgG GMT at 4 weeks (28 days) post Vi-DT (MD) is equivalent to GMT of Vi-DT (SD) in adults using equivalence margin of GMT ratio of [0.67, 1.5]

If the two-tailed 95% confidence interval of the ratio of GMT estimate of Vi-DT(MD) over GMT of Vi-DT(SD) is located within [0.67, 1.5], Vi-DT(MD) is equivalent to Vi-DT(SD) in terms of GMT of immunogenicity with two sided significance level of 0.05.

The statistical hypothesis for the secondary objective is to demonstrate equivalence of two Vi-DT formulations (MD vs. SD) using seroconversion.

- Seroconversion rates of anti-Vi IgG ELISA antibody titres at 4 weeks (28 days) from baseline(D0) of Vi-DT(MD) is equivalent to seroconversion rate at 4 weeks of Vi- DT(SD) in adults using equivalence margin of 10%

If the two tailed 95% confidence interval of the estimate of difference of seroconversion rate between Vi-DT(MD) and Vi-DT(SD) at 4 weeks (Day 28) is located within [-10%, 10%], Vi-DT(MD) is equivalent to Vi-DT(SD) in terms of sero-conversion rate which is defined as 4 fold increase of immunogenicity from baseline with significance level of 0.05.

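### The stated power of 94% (GMT) and 95% (seroconversion) does not follow from the protocol's own 95% CI rule and dropout, which give about 84% and 86–88%

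*Protocol*

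**What the plan says.** Section 11.1, repeated under Statistical Considerations in the synopsis, sizes the trial on the adult stratum: "The immunogenicity subset in adult participants, N=250 per group", "will provide 94% power to show equivalence of geometric mean titres (GMT) of anti-Vi IgG". The listed inputs are a margin of [0.67, 1.5], CV 2.0, type 1 error 0.05 and 10% dropout. For the secondary endpoint it adds: "This sample size of N=250 will provide 95% power, for equivalence tests of seroconversion rate", with a 90% rate, a margin of ±10 points and type 1 error 0.05. No true GMT ratio or true difference is stated.

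The decision rule is in section 11.3: "If the two-tailed 95% confidence interval of the ratio of GMT estimate of Vi-DT(MD) over GMT of Vi-DT(SD) is located within" the margin, equivalence is declared at a two-sided level of 0.05. The synopsis and section 11.5.4 give the same interval rule for GMT. The synopsis and sections 11.3 and 11.5.5 give the matching one for seroconversion.

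The 250 per group is an enrolment figure. The group allocation table and Table 1 list it as such, and section 5.2 says "Adult participants (N=500) will be followed up additionally for immunogenicity 4 weeks post vaccination". Section 11.5.1 does not impute missing titres in the main analysis.

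The text on age strata reassignment after Table 2 adds adults, because Day 28 samples were lost to the lockdown, so as to "keep the initial planned statistical power for immune equivalence test as planned initially". It gives no new adult number.

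**The concern.** Requiring a two-tailed 95% interval to sit inside an equivalence margin is the same as passing two one-sided tests at 0.025 each. It is stricter than two tests at 0.05 each, which correspond to a 90% interval. Participants who drop out also contribute no titre to the main analysis. A power figure for this design should reflect both, and the printed figures look too high to do so.

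At stake is the risk the sponsor believes it is taking on the primary objective. The same planned power is also the stated benchmark for moving places from the two paediatric strata to adults, so a benchmark that the design does not meet gives no usable adult target.

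**Working it through.** **Inputs (section 11.1 unless noted)**
- 250 enrolled per arm, allocated 1:1. With 10% dropout, 250 × 0.9 = 225 evaluable.
- CV 2.0, so the SD of ln titre is √ln(1 + 2²) = √ln 5 = 1.2686.
- GMT margin: ln 0.67 = −0.4005 and ln 1.5 = 0.4055.
- Rule: 95% CI inside the margin (section 11.3), so 0.025 per side, z = 1.960.
- Assumed here because the protocol states neither: true GMT ratio 1 and true seroconversion difference 0. These are close to the most favourable values.

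**GMT formula.** SE = 1.2686 × √(2/n). Power = Φ(0.4055/SE − z) + Φ(0.4005/SE − z) − 1.

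*Reproducing the stated 94%.* With n = 250, SE = 0.1135, and the margins are 3.573 and 3.529 standard errors away. At 0.05 per side (z = 1.645): Φ(1.928) + Φ(1.885) − 1 = 94.3%. This matches.

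*Under the protocol's rule.* With n = 225, SE = 0.1196, and the margins are 3.390 and 3.348 standard errors away. At 0.025 per side: Φ(1.430) + Φ(1.388) − 1 = 84.1%, or 83.9% with the t distribution.

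| Evaluable per arm | 90% CI (0.05 per side) | 95% CI (0.025 per side) |
|---|---|---|
| 250 | 94.3% | 88.7–88.8% |
| 225 | 91.4–91.5% | 83.9–84.1% |

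(Ranges: t-based to normal.)

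A second route also gives 94%. Testing only the lower bound, once, at 0.025 with n = 250 gives Φ(1.569) = 94.2%, or 94.1% with t. It ignores the upper bound and dropout.

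*Sensitivity at 225, 95% CI:* a true ratio of 0.95 gives 79.8%, and 0.90 gives 68.2%. Reaching 94% under the 95% CI rule takes 293 evaluable per arm (normal) or 294 (t). Dividing by 0.9 gives about 326–327 enrolled.

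**Seroconversion formula.** SE = √(2 × 0.9 × 0.1/n). Power = 2Φ(0.10/SE − z) − 1.
- n = 250, 0.05 per side: 0.10/SE = 3.727 and power = 96.3%. Exact enumeration with score (Farrington–Manning) limits gives 95.7%. Both are near the stated 95%.
- n = 225, 0.05 per side: 94.1% (normal), 93.4% (score).
- n = 250, 0.025 per side: 92.3% (normal), 92.1% (Wald), 90.8% (score).
- n = 225, 0.025 per side: 0.10/SE = 3.536 and power = 88.5% (normal), 88.1% (Wald), 87.1% (Newcombe), 86.3% (score).

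No two-bound calculation at 0.025 per side reaches 95%, with or without dropout.

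**The case against.** Several points can fairly be made on the other side.

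- **The cause is not known.** A reader might infer that the sponsor assumed a 90% CI and no dropout. The documents do not support that. The 94% also comes from a single one-sided 0.025 test at 250 per arm. For seroconversion, 225 per arm with a 90% CI gives 94.1%, so dropout may have been counted there. What stands is that no candidate route matches the stated rule with dropout.
- **Dropout is named only with the GMT calculation.** The seroconversion sentence in section 11.1 does not mention it, so 86–88% carries that assumption across. Without it the figure is 91–92%, still short of 95%.
- **The seroconversion input is cautious.** Section 3.2 reports that all Vi-DT recipients in the phase I trial seroconverted. At a true rate of 95%, power at 225 per arm under the 95% CI rule is 99.6%. The shortfall on this secondary endpoint therefore has little practical weight, though the printed figure is still wrong for its stated inputs.
- **Power could be better than 84%.** The protocol calls CV 2.0 conservative, and section 11.5.1 allows adjustment for baseline titre if necessary. If covariates explained 10% or 20% of the log-titre variance, GMT power at 225 would be about 88.7% or 92.8%. These are illustrations only, since the protocol gives no correlation and section 11.5.4 names only group and strata as covariates.
- **The redistribution has its own reason.** A reader might infer that the wrong power figure drives adult enrolment. The text attributes the change to Day 28 samples that could not be drawn, and those needed replacing whatever the planned power was. It does not cite 94%.

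**Conclusion.** The point holds as a numerical inconsistency. Under the protocol's own rule and dropout, GMT power is about 84%, not 94%, and seroconversion power is about 86–88%, not 95%. Even with all 250 per arm evaluable, the figures are about 89% and 91–92%.

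The GMT result rests on CV 2.0, a true ratio of 1 and no gain from covariates. On those terms the chance of missing the primary objective is about 16% rather than 6%. It is a conditional figure: a true ratio away from 1 raises it, and baseline adjustment could lower it by an amount the protocol does not let one compute.

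It would be wrong to read this as a flaw in the test itself. The 95% CI rule is stated consistently, type I error is unaffected, and power under the stated assumptions stays above 80%. The power actually reached after the redistribution cannot be computed, because no new adult number is given.

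**What to change.** Keep the 95% CI rule. In section 11.1 and the synopsis, restate power for 225 evaluable per arm as about 84% (GMT) and 86–88% (seroconversion, naming the interval method). State alongside these the per-side alpha of 0.025, the assumed true ratio of 1 and the assumed true difference of 0.

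In the age strata reassignment text, express the adult target as evaluable Day 0/Day 28 pairs per arm, with the power that number gives under the 95% CI rule. The sponsor can then see what the added adults achieve.

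The cost is wording and a less favourable stated power. The correction requires no extra participants. Holding to 94% for GMT would be a separate decision, needing about 293–294 evaluable per arm on the same assumptions.

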## 11.2 STATISTICAL ANALYSIS PLAN

The statistical analysis will focus on comparisons of immunogenicity of Vi-DT (MD; Group A) and Vi-DT (SD; Group B) at 4 weeks post vaccination. Safety of Vi-DT will be assessed by descriptively comparing incidence of common solicited, unsolicited and serious AE between Vi-DT and Control and any incidence of unexpected AE. A primary analysis will be performed after all participants complete week 4 visit post test/control vaccine dose in order to initiate the test vaccine licensure process. Immunogenicity and safety data up to week 4 will be included in this analysis and this will be done in a way so that the study and study personnel remain blinded to the allocation of test/control vaccine until the end of the study. The final analysis will be performed when all participants complete week 24 visit. Immunogenicity and safety data up to week 24 will be included in the final analysis.

Additional statistical analysis details will be described in the statistical analysis plan (SAP) (which will be finalized prior to database lock) and any deviation(s) from the original SAP will be described and justified in the final study report.

## 11.3 STATISTICAL HYPOTHESES

The statistical hypothesis for the primary objective is to demonstrate equivalence of two Vi-DT formulations (MD vs. SD) using GMT.

- Anti-Vi IgG GMT at 4 weeks (28 days) post Vi-DT (MD) is equivalent to GMT of Vi-DT (SD) in adults using equivalence margin of GMT ratio of [0.67, 1.5]

If the two-tailed 95% confidence interval of the ratio of GMT estimate of Vi-DT(MD) over GMT of Vi-DT(SD) is located within [0.67, 1.5], Vi-DT(MD) is equivalent to Vi-DT(SD) in terms of GMT of immunogenicity with two sided significance level of 0.05.

The statistical hypothesis for the secondary objective is to demonstrate equivalence of two Vi-DT formulations (MD vs. SD) using seroconversion.

- Seroconversion rates of anti-Vi IgG ELISA antibody titres at 4 weeks (28 days) from baseline(D0) of Vi-DT(MD) is equivalent to seroconversion rate at 4 weeks of Vi- DT(SD) in adults using equivalence margin of 10%

If the two tailed 95% confidence interval of the estimate of difference of seroconversion rate between Vi-DT(MD) and Vi-DT(SD) at 4 weeks (Day 28) is located within [-10%, 10%], Vi-DT(MD) is equivalent to Vi-DT(SD) in terms of sero-conversion rate which is defined as 4 fold increase of immunogenicity from baseline with significance level of 0.05.

#### 11.4 ANALYSIS DATASETS

The Full Analysis set (FAS) is a modified intention-to-treat (m-ITT) analysis set that will include all participants randomized in the study who received at least one dose of investigational vaccines. This data set will be used for demographic information and safety analysis.

The immunogenicity analysis set is a subset of FAS of those who is randomized, received at least one dose of investigational vaccines and have at least one post-baseline immunogenicity data available.

The per-protocol (PP) analysis set will be a subset of the immunogenicity analysis set who do not have protocol violations (defined as major deviation from the protocol compromising the scientific integrity of the study) with regards to the inclusion/exclusion criteria, are compliant with study procedures, completed all visits as scheduled and received the correct vaccinations.

The immunogenicity analysis set will be used for the primary analysis of the immunogenicity endpoints. A sensitivity analysis using the PP analysis sets will be conducted for the primary and secondary immunogenicity endpoints.

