## 5 STUDY DESIGN

### 5.1 STUDY ENDPOINTS

#### Primary Endpoints

- Geometric Mean Titers (GMT) of anti-Vi IgG at 4 weeks (28 days) after vaccination of Vi-DT(MD)/ Vi-DT (SD) [18-45 year age stratum]

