## 7.9 PROTOCOL DEVIATIONS

A protocol deviation is any non-compliance with the clinical trial protocol or GCP by the participant, the investigator, or the study site staff. It is the responsibility of the site investigator to use continuous vigilance to identify and report all major protocol deviations to site IRB and sponsor. Minor protocol deviations could be reported to IRBs along with periodic study report submission as per local IRBs requirements. The site investigator is responsible for knowing and

adhering to the site IRB requirements. The IVI Study Medical Monitor will report all protocol deviations to IVI IRB.

Major deviations are defined as those jeopardize the safety or rights of the participant or the scientific integrity of the study which may be applicable to cases listed below.

- Violation of inclusion and exclusion criteria
- Vaccination with wrong vaccine as defined in the protocol
- Visit outside window for the immunogenicity assessment after discussion with the study medical monitor
- Missed samples for immunogenicity

Major protocol deviations thought to affect the scientific integrity of the study will be reported and discussed with investigator, monitor, sponsor, and statistician for their exclusion from the per protocol analysis. For minor protocol deviations considered not to affect the scientific integrity of the study, the extent of deviation or delay as well as reason will be accurately documented.

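### Equivalence is decided only on an m-ITT-type set that keeps major deviations; the per-protocol set has no part in the decision rule

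*Protocol*

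**What the plan says.** **Endpoint.** Section 5.1 defines the primary endpoint as "Geometric Mean Titers (GMT) of anti-Vi IgG at 4 weeks (28 days) after vaccination", compared between the multi-dose (MD) and single-dose (SD) formulations in adults. Table 2 and section 7.6.3 schedule one post-vaccination blood draw, at V4, Day 28 ±3.

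**Deciding set.** Section 11.4 builds the immunogenicity set from a parent set: "The Full Analysis set (FAS) is a modified intention-to-treat (m-ITT) analysis set". A participant enters it if randomised, dosed, and found to "have at least one post-baseline immunogenicity data available". Then: "The immunogenicity analysis set will be used for the primary analysis of the immunogenicity endpoints".

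**PP set.** Freedom from eligibility violations is a condition of PP only. So are the requirements that the participant "completed all visits as scheduled and received the correct vaccinations". Its role is limited: "A sensitivity analysis using the PP analysis sets will be conducted for the primary and secondary immunogenicity endpoints".

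**Deviations.** Section 7.9 lists as major the violation of entry criteria, "Vaccination with wrong vaccine as defined in the protocol", and "Visit outside window for the immunogenicity assessment after discussion with the study medical monitor". The consequence it provides for is possible exclusion from the per-protocol analysis, and from no other.

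**Decision rule.** Sections 11.3 and 11.5.4 declare equivalence when the two-sided 95% CI for the GMT ratio lies within [0.67, 1.5]. Neither mentions PP.

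**The concern.** In a superiority trial, an m-ITT set that keeps deviations usually works against the sponsor's claim. In an equivalence trial it can work for the claim. If some participants randomised to MD receive SD and the reverse, and all are analysed as randomised, the two arms look more alike than the formulations are. The protocol regards a wrong vaccination as serious enough to list as major, but keeps those titres in the only analysis that decides equivalence.

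At stake is the bridging claim for MD against SD. Section 11.2 runs the primary analysis after the week 4 visits so that licensure can begin. As written, the primary set could satisfy the margin while the PP interval crosses it, and the rule would still read as equivalence. The protocol itself fixes this through its choice of primary set, its entry conditions and the subordinate role of PP. It is not a detail left to a statistical analysis plan.

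**Working it through.** **Inputs from section 11.1:** 250 adults per arm, CV 2.0, 10% dropout (so 250 × 0.9 = 225 evaluable), stated power 94%. **From 11.3:** margin [0.67, 1.5], 95% CI rule. **Assumed, not in the documents:** the fraction f of each arm given the other formulation.

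**Step 1. Scale.** SD of ln titre = √ln(1 + 2²) = 1.2686. With n = 225, SE = 1.2686 × √(2/225) = 0.1196.

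**Step 2. The plan's own power.** With true log ratio θ = 0, power = Φ((ln 1.5)/SE − z) − Φ((ln 0.67)/SE + z).

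| n per arm | Rule | Power |
|---|---|---|
| 250 | 0.05 per side (90% CI) | 94.3% |
| 250 | one-sided 0.025 against 0.67 only | 94.2% |
| 250 | 95% CI within the margin | 88.8% |
| 225 | 95% CI within the margin | 84.1% |

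The stated 94% is reproduced only without dropout and under a rule other than the one in 11.3. The point made here does not depend on that figure, but the 84% is the right baseline for costing the fix.

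**Step 3. Effect of MD/SD swaps, analysed as randomised.** The mean log titre is (1 − f)μ_MD + fμ_SD in one arm and (1 − f)μ_SD + fμ_MD in the other. The difference is (1 − 2f)θ, so the log ratio shrinks by the factor 1 − 2f. The variance gains f(1 − f)θ², which is negligible here.

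**Step 4. False equivalence at the margin.** Set the true ratio at 1.5 (θ = 0.4055), n = 225, 95% CI rule.

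| f per arm | Expected ratio, 1.5^(1−2f) | P(declare equivalence) |
|---|---|---|
| 0 | 1.500 | 2.5% |
| 0.5% | 1.494 | 2.7% |
| 1% | 1.488 | 2.9% |
| 2% | 1.476 | 3.4% |
| 5% | 1.440 | 5.2% |
| 10% | 1.383 | 9.9% |

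For example, at f = 2%: (0.4055 − 0.96 × 0.4055)/0.1196 − 1.960 = −1.824, and Φ(−1.824) = 3.4%. Of 225 adults, 2% is about 5 and 5% is about 11.

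**Step 5. Other wrong-vaccine patterns.**
- Control vaccine given by mistake to the same fraction of both arms shrinks the log ratio by 1 − f. At f = 2% the ratio of 1.5 becomes 1.488 and the error rate is about 2.9%.
- Control vaccine given by mistake in one arm only can push the ratio away from 1. With f = 2% and an assumed 50-fold lower titre, a true ratio of 1.00 becomes 50^(−0.02) = 0.925, and power falls from 84% to 70%. The ratio is 0.955 if the titre is 10-fold lower and 0.900 if it is 200-fold lower.

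**Step 6. Power cost of a second set.** If five per arm are excluded, n = 220 and SE = 0.1210. Power = Φ(1.392) − Φ(−1.351) = 0.918 − 0.088, about 83%. Requiring both sets to succeed cannot exceed the power in the smaller set, and should lie close to it because the two sets overlap almost completely.

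**The case against.** **The entry condition is less open than it sounds.** A reader might infer that titres from any day after vaccination can enter. Only V4 is scheduled for a post-vaccination draw, and section 5.2 says that samples missed in the lockdown are not taken later. In practice the condition admits a V4 sample of any timing. This stands.

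**Off-window samples are not shown to favour equivalence.** Timing noise unrelated to arm widens the interval and makes equivalence harder to declare. It blurs what is meant by a 4-week titre, but the bias toward 1 does not come from it. This stands.

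**The direction is conditional.** A reader might infer that every wrong-vaccine titre pulls the ratio toward 1. The swap result needs analysis by randomised arm, which the protocol implies through m-ITT but never states. Under analysis by vaccine received, the dilution from swaps disappears. Control vaccine given in one arm only can act the other way. This stands.

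**Swaps may be rare.** Vials are labelled MD or SD with separate drug codes (6.1.2). A dedicated unblinded vaccinator works from the allocation list and writes the randomisation number on the vial and the accountability log (5.3.1), and an unblinded monitor is in place (6.1.6). The documents give no error rate, and below about 1% the inflation is small. This stands too.

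**A clean analysis is already planned.** PP is run for both immunogenicity endpoints, so a discordant result would be visible. It would be visible but would decide nothing, because 11.3 and 11.5.4 do not refer to it. That part of the concern survives.

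**Conclusion.** The concern holds in limited form. The protocol decides equivalence solely on a set that keeps cases its own section 7.9 calls major deviations, and gives the set that removes them no role in the decision. In an equivalence test that is an avoidable weakness.

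The size is modest: false equivalence at the margin rises from 2.5% to 2.9%, 3.4% or 5.2% for swap rates of 1%, 2% or 5% per arm. These figures assume analysis as randomised, symmetric MD/SD swaps, CV 2.0, 225 evaluable per arm and a normal approximation. The swap rates are assumptions. No size has been calculated for eligibility violations.

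The documents do not support a claim that the trial will be biased toward equivalence, that late samples favour it, or that no clean analysis exists. Minor to moderate.

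**What to change.** - **Section 11.4:** define a Day 28 per-protocol set of participants who were eligible, received the assigned vaccine and have a V4 sample within Day 28 ±3. Membership should not depend on V5 or other visits and should be fixed before any by-group data are seen.
- **Sections 11.3 and 11.5.4:** declare equivalence only if the 95% CI for the GMT ratio lies within [0.67, 1.5] in both the immunogenicity set and this Day 28 set.

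The present PP set cannot serve for this. It requires every visit as scheduled, and V5 at week 24 has not taken place when the week 4 analysis is run. Removing the medical-monitor discussion from the window item in 7.9 would not be enough either, because that list governs exclusion from PP and leaves the primary set unchanged.

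The cost is a wording amendment and a small loss of power: about 84% at 225 per arm under the 95% CI rule, and about 83% if five per arm are excluded.
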